##### Quantitative sensory testing

A battery of standardised sensory tests quantifies the function of the somatosensory system. QST tests the characteristics of various sensation and nociceptive processes as representative of afferent nerve fibres and central pathways performance. The whole assessment lasts for 1 hour, and it consists of six sensory tests, which are measured in seven different predefined body locations: one training location to familiarise the patient with the tests, the most painful location (as pointed out by the patient), and five control locations. See online supplementary material 1 for full description of body locations. The standardised instructions of the sensory tests are read to the patient at each test performance. Of the tests, five consist of mechanical stimuli based on and performed following the QST examination of the German Research Network on Neuropathic Pain (DFNS) protocol,^32^ and one for CPM following the Nijmegen-Aalborg Screening QST protocol.^33 43^ Overall, the DFNS protocol has shown good test–retest (mean r=0.86) and interobserver reliability (mean r=0.83) in patients with affections in the somatosensory system either with or without pain.^44^ For the purpose of avoiding bias due to the order of the measurements and locations, a counterbalancing procedure is established, which accounts for the locations and the measurements to be made. This procedure provides three different assessment order groups, all of which begin with the measurements at the training location and end with the CPM test. An additional counterbalancing procedure has been made for allocating patients to these assessment order groups (either 1, 2, or 3). Every nine patients, a different allocation order is performed to ensure a similar amount of QST assessments per group. All assessors are trained in the QST protocol. The following sensory tests are performed:

10.1136/bmjopen-2019-031592.supp1Supplementary data

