*Dynamic mechanical allodynia* (*DMA*)—to test the presence of abnormal stimuli-evoked pain—is assessed with a soft brush (SENSElab, Brush-05, Somedic, Hörby, Sweden) that is swiped 1–2 cm over the skin. This is performed on a single repetition and on a train of three repetitions (wind-up response). At each of the seven body locations (see online supplementary material 1) it is recorded whether the patients feel the sweeping and its pain intensity with a numeric rating scale (NRS) ranging from 0 (no pain) to 100 (most intense pain imaginable) for both the single swipe and the series.^45 46^ The DMA (ratio) is calculated as: DMA=(NRS-3/NRS-1). If NRS-1 is 0, the DMA for that location cannot be calculated and it will be registered as a missing value. The DMA test according to the DFNS protocol has shown to have good test–retest (r=0.87) and interobserver reliability (r=0.79).^44^

*Mechanical pain threshold* (*MPT*)—to test the ability to perceive sharp, pricking or stinging stimuli—is assessed with a set of standardised weighted pinprick stimulators with seven different intensities (the PinPrick Stimulator Set, MRC Systems, Germany) and with a modified method of limits. Starting at the lowest intensity (8 mN), it progressively increases until patients report the stimulus to change from touch to painful (sharp, pricking or stinging). The intensity of the pinprick that produces the first painful stimulus in millinewtons is recorded in each of the seven locations (see online supplementary material 1).^46–49^ The MPT test according to the DFNS protocol has shown to have good test–retest (r=0.80) and interobserver reliability (r=0.80).^44^

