*Wind-up ratio* (*WUR*)—to test the nervous system’s painful stimuli temporal summation or responsiveness to repeated noxious stimuli. Such test is assessed with a suprathreshold pinprick stimulator of 256 mN (the PinPrick Stimulator Set, MRC Systems, Germany), which is applied on a single repetition and on a train of 10 repetitions in an area of 1 cm^2^ with intervals of 1 s (wind-up response). The pain intensity measured with an NRS ranging from 0 (no pain) to 100 (most intense pain imaginable) for both the single repetition and the series is recorded in each of the seven body locations (see online supplementary material 1).^50 51^ The WUR (ratio) is calculated as: WUR=(NRS-10/NRS-1). If NRS-1 is 0, the WUR for that location cannot be calculated and it will be registered as a missing value. The WUR test according to the DFNS protocol has shown to have poor test–retest (r=0.67) and interobserver reliability (r=0.56).^44^

*Mechanical detection threshold* (*MDT*)—to test the ability to detect light touch—is assessed with a standardised set of von Frey filaments (OptiHair2-Set, Marstock Nervtest, Germany) with a modified method of limits.^52 53^ Starting at the intensity of 16 mN, the stimulus application progressively decreases until patients do not report any sensation. The intensity of the filament that is not perceived in millinewtons is recorded in each of the seven body locations (see online supplementary material 1).^54^ The MDT test, according to the DFNS protocol, has shown to have good test–retest (r=0.90) and interobserver reliability (r=0.89).^44^

*Pressure pain threshold* (*PPT*)—to test the ability to perceive pressure pain stimuli on muscles—is assessed with an electronic pressure algometer (Force Ten FDX, Wagner Instruments, USA). With this tool, the pressure in the contact point (1 cm^2^ tip) is progressively but steadily increased until patients report to feel pressure change towards painful (burning, drilling or aching). The intensity in newtons when pressure becomes painful and its pain intensity with an NRS ranging from 0 (no pain) to 100 (most intense pain imaginable) scale is recorded in each of the seven body locations (see online supplementary material 1).^32^ The PPT test according to the DFNS protocol has shown to have good test–retest (r=0.88) and interobserver reliability (r=0.84).^44^

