### Analyses

Data records from the different tests and questionnaires will be collected and merged into one database. The database management will be done by the project team and handled according to the internal regulations of the UMCG. The analyses of the study will be performed with SPSS software version 22.0 (IBM).

Before any analysis, data will be prepared:

Variables need to be calculated: body mass index; DMA, WUR and CPM tests (see the Methods and analyses section, Measurements: CS measurements); PDI, Rand36-PF, PCS, BSI and IEQ questionnaires.HRV: data will be preprocessed to correct for any artefacts that may be present at the beginning or at the end of the recording.QST: the overall value of each sensory test is the mean at the most painful location and the five control locations together, provided that at most two locations are missing.To perform the analyses to respond to objective 3, delta scores are computed (difference in scores between baseline and discharge) for CS, functioning and those confounder variables which are also measured at the same time points as the main measurements.

Proxies of the main measurements were selected to perform analyses. CS variables are: the sum score of CSI part A and the RMSSD for HRV. For QST, no variables are predefined, variables that correlate most strongly with each of the functioning measures will be selected. Functioning variables are: the maximal weight lifted for lifting capacity, the VO_2_max/kg for the maximal aerobic capacity, the daily vector magnitude (VM) counts for PA and the average score of Rand36-PF for reported physical functioning.

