The presence of missing data will be checked. If a variable has more than 10% of missing data cases, its distribution will be further examined. When the distribution of missing data is missing completely at random, analyses with pairwise deletions are planned. If data are not missing completely at random, other suitable solutions will be applied such as multiple imputation.^91^ Regarding the presence of outliers, cases at 3 SD from the mean will be considered as outliers. Their influence will be measured using Cook’s distance and leverage values. When the outliers are not statistically influential and/or there is rationale for the outlier, no further actions are planned. The descriptive statistics of the sample characteristics and main test results will be at this point calculated; numerical variables as mean and SD in normally distributed data and as median and IQR (25–75)) in non-normally distributed data, and categorical variables as counts and percentage of each category level.

*Statistical approach for objective 1: to analyse the association between instruments assessing reference symptoms and signs attributed to CS.* Multiple partial correlation analyses will be performed and corrected for potential confounders. CS measurements will be the main variables and sex and age will be covariates. Additional covariates may enter the partial correlations based on their correlation coefficient with CS instruments and if p<0.01. Results will be reported as correlation coefficients (Pearson’s r and/or Spearman’s rho) and p values, with and without controlling for covariates. The significance level for all analyses is established at 0.01, to account for the potential type I error due to the multitude of partial correlation analyses.
*Statistical approach for objective 2: to analyse whether reference symptoms and signs attributed to CS are associated with functioning measurement outcomes.* First, multiple correlation analyses, followed by multiple regression analyses with data obtained at baseline, will be performed. Each of the main outcomes from functioning measurements will be introduced in the models as dependent variable, CS measurements as independent variables, and sex, age and other demographic characteristics and/or test-related variables as potential confounders and/or moderators.

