There are circumstances that might have influenced the results, in spite of the team’s efforts to obtain the most extensive insights of CS and its association with functioning. To begin with, it should be considered that patients participating in the study are volunteers. Moreover, the exclusion criteria, despite being based on patients’ files, are also dependent on doctor’s judgement. The impact of these circumstances is so far unknown to the authors. Likewise, given the CAU design of the study the choice of measurements has to be feasible and compatible with the regular clinical procedures. As a consequence, the functional MRI, a commonly mentioned instrument to measure CS, could not be performed in the study. The HRV, on the other hand, although less often used, can be an insightful and innovative approach to the assessment of one of the indicators of CS. Additionally, the sample sizes are estimated a priori for the analyses due to insufficient previous studies and, therefore, they are of exploratory nature and used as a guide. Also, despite the efforts of the team to promote the study participation and participant retention, it is likely that patient recruitment may be slower than anticipated and that the patient may not have a complete follow-up. However, since the measurement period is ample, the calculations are vigilantly made with generous margins (see the Methods and analyses section, Sample size), and the literature related to the topic has shown smaller sample sizes.^25 28 110^ We remain positive about the sample size and expect to have more than enough participants to perform analyses with sufficient power. Also, for comparability purposes, measurements are planned to take place within 3 weeks from the Pain Rehabilitation team’s baseline and discharge assessments. The CSI, PDI and psychological screening questionnaires during baseline assessment are sent to be filled up 6 weeks before the rest of the measurements are obtained, a time distance due to waiting list time. Measurements are expected to be comparable to the rest of measurements at baseline, since no important changes are foreseen in patients regarding medication, surgery or personal conditions during this time, and questionnaires have shown to have good clinimetric properties. As opposed to the limitations presented, given the large amount of correlations in the multiple correlation analyses and the risk of type I error, a more strict significance level was applied, that is, 0.01. Also, for the QST the proxy will be selected per functioning outcome to obtain the most informative somatosensory measurement for each of the functioning measurements. We are confident that the results obtained will provide meaningful and valuable information.

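### The QST proxy is chosen by largest correlation with no allowance for the number of patients behind it, which can favour a sparsely observed test, most plausibly DMA

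*Protocol article*

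**What the plan says.** The Analyses section names fixed proxies for the Central Sensitisation Inventory (CSI) and for heart rate variability (RMSSD). It names none for QST: "variables that correlate most strongly with each of the functioning measures will be selected". The Discussion presents this as deliberate, since "the proxy will be selected per functioning outcome to obtain the most informative somatosensory measurement". The rule carries no minimum number of patients, no common sample and no measure of precision.

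The QST section says of the battery that "it consists of six sensory tests": DMA, MPT, WUR, MDT, PPT and CPM. DMA "is assessed with a soft brush" and is scored as the pain rating after three swipes divided by the rating after one. "If NRS-1 is 0, the DMA for that location cannot be calculated and it will be registered as a missing value". The wind-up ratio has a similar rule ("If NRS-1 is 0, the WUR for that location cannot be calculated"), but its stimulus is a 256 mN suprathreshold pinprick. The other four tests have no zero-denominator rule on a pain rating.

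Under Analyses, the overall value of each test is the mean over the most painful site and five control sites, "provided that at most two locations are missing". A patient therefore needs a computable value at four or more of six sites. For missing data, "When the distribution of missing data is missing completely at random, analyses with pairwise deletions are planned"; otherwise another solution, such as multiple imputation, is to be used.

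**The concern.** Correlations from different numbers of patients are not on the same footing. With no true association, the spread of r is about 1/√n, so a test observed in few patients produces large values of |r| more often by chance. A rule that takes the largest |r| leans towards the test with the fewest data.

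This is separate from the optimism of picking a maximum, which arises even when all tests have the same n. Here the ranking statistic itself is not comparable between candidates.

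DMA is the obvious candidate. It has a value only if one brush stroke hurts at four or more of six sites, five of them control sites. The QST section treats brush-evoked pain as abnormal, and patients with sensitivity alterations at measurement sites are excluded (Participants). If DMA is chosen because it is sparse, the regression for that outcome may rest on a small subset, which also weakens the CSI and RMSSD coefficients. Different functioning outcomes could then be answered in different sets of patients.

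**Working it through.** **1. The plan's own figures (Sample size section).** Three tested predictors of eight, α = 0.05, power 0.80 and a medium effect, taken here as f² = 0.15 (an assumption; the article gives no value). With a noncentral F test on 3 and N − 9 degrees of freedom and noncentrality f² × N, the smallest N is 77, as stated. Allowing for 30% loss, 77 / 0.70 = 110, as stated.

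**2. How often DMA can be computed.** The article gives no rate. As an illustration, let each of six sites independently have probability p of a non-zero single-swipe rating. The chance of four or more usable sites is the upper binomial tail:

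| p per site | P(≥ 4 of 6) | Patients of 110 |
|---|---|---|
| 0.3 | 7% | 8 |
| 0.4 | 18% | 20 |
| 0.5 | 34% | 38 |
| 0.6 | 54% | 60 |
| 0.7 | 74% | 82 |
| 0.9 | 98% | 108 |

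Sites within a patient are probably correlated, which would change these figures. The table shows only that heavy loss is plausible unless brushing hurts at most sites.

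**3. Spread of r with no association.** The standard error is about 1/√(n − 1): 1/√109 = 0.10 at n = 110, 1/√29 = 0.19 at n = 30 and 1/√19 = 0.23 at n = 20.

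**4. How often DMA has the largest |r|.** Simulation with six tests, five complete at n = 110 and DMA observed in n patients, 40,000 runs per setting. The fair share is 1/6 = 17%.

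| DMA n | No association anywhere | Other five tests truly r = 0.25, DMA 0 |
|---|---|---|
| 20 | 54% | 14% |
| 30 | 45% | 7% |
| 60 | 29% | 1% |
| 77 | 23% | < 1% |
| 88 | 21% | < 1% |
| 99 | 19% | < 1% |

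The tests are independent of one another here. A correlation of 0.3 between tests barely changes the no-association column; it raises the last column slightly (for example to 2% at n = 60).

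Ranking on Fisher z × √(n − 3) instead of |r| brings the no-association share back to about 17% at every n.

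**5. Power if the model is fitted only in patients with DMA.** Same test as in step 1:

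| n | Power |
|---|---|
| 110 | 93% |
| 77 | 80% |
| 55 | 63% |
| 30 | 34% |
| 20 | 20% |

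At baseline there is slack down to n = 77. At discharge the planned number is already 77, and a DMA change score needs a computable value at both visits, so any loss takes power below 80%.

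**The case against.** **The missing rate is not in the article.** A reader might infer that DMA is the test with the most missing data and will usually be selected by chance. The text does not support that as a fact. It gives no rate for any test, and the Participants section points both ways: sensitivity alterations at measurement sites are excluded, but patients with fibromyalgia and similar comorbidities stay in. This stands, so the size is conditional.

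**The harm needs an intermediate range.** If almost nobody has a DMA value, an eight-predictor model cannot be fitted and the problem is visible. If 10-30% are missing, the excess is 19-23% against 17%. If the other tests carry real signal at r = 0.25, DMA is rarely chosen except at very small n. This also stands.

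**A p < 0.01 level is set for correlation analyses.** If a proxy also had to reach it, DMA would be chosen in only about 1% of outcomes. But the article gives that level as protection against type I error over many correlations and does not tie it to proxy selection. The rule as written is strength of correlation alone.

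**The regression need not shrink.** A reader might infer that choosing DMA necessarily cuts the regression sample. It does so only if patients without DMA are left out. DMA is missing because of the pain rating itself, so it is not missing completely at random, and the plan then points to another solution such as imputation. That is right as far as it goes. But a ratio with a zero denominator is undefined rather than unobserved, so imputing it has no clear meaning. An imputed correlation would also still draw on the same few observed pairs.

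**The limits are partly disclosed.** The article says that its selections of measurements may influence results and calls its sample sizes exploratory. It does not mention unequal numbers behind the correlations.

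**Conclusion.** The concern holds in a conditional form. The rule compares correlations that may rest on very different numbers of patients, and the article's own scoring makes this likely for DMA. With DMA available in about 20-60 of 110 patients and no true associations, it would be picked in about 54% to 29% of outcomes instead of 17%. The excess is minor at 10-30% missing or when the other tests truly correlate at about 0.25. If patients without DMA are then dropped, power for the planned three-of-eight test falls from 93% at n = 110 to 63% at n = 55 and 20-34% at n = 20-30.

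These figures assume f² = 0.15, independent tests and complete data on the other five. The number of patients with DMA is an assumption shown as a range. The defect in the rule does not depend on that number, but its practical size does. A change is worth making because it costs little.

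**What to change.** In the proxy paragraph of the Analyses section, add that a QST test can serve as proxy only if its overall value is available in a prespecified minimum share of patients, for example 90%. This would be a new eligibility limit: the existing 10% figure for missing data only triggers further examination. Rank the eligible tests on one common sample, or on Fisher z × √(n − 3), and describe ineligible tests separately.

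Both parts are needed. Fisher-z ranking alone removes the selection bias, but it would still pick DMA about 17% of the time under no association, with the sample loss that may follow.

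The cost is a sentence or two in the plan. The downside is that DMA, and possibly WUR, as now scored may only be described and not enter the regressions.

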##### PA levels

The objective measurements of PA levels are obtained by means of an accelerometer (ActiGraph GT9X Link, ActiGraph, Pensacola, FL, USA). The accelerometer is a small and light device that monitors wearers’ daily PA and energy expenditure. Participating patients wear the accelerometer attached at their hip level for 1 week continuously during walking hours, in order to ensure the minimum of 4 full-day recordings as recommended by activity monitoring reviewers and experts.^68 69^ Different algorithms are chosen from the software provided by the manufacturer, ActiLife6 (ActiGraph, Pensacola, Florida, USA), to discriminate between low PAs and split patients in three activity intensity categories (sedentary, light and moderate)^70^ and to obtain patients’ energy expenditure in kilocalories^71^ and MET.^72^ The daily and weekly time in hours and percentage of time spent in each of the activity intensity categories as well as the estimated energy expenditure in both kilocalories and MET are collected.

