*Statistical approach for objective 3: to analyse whether changes (between baseline and discharge) in reference symptoms and signs attributed to CS are related to changes in each of the functioning measurement outcomes.* A similar approach to objective 2 will be performed: first, multiple correlation analyses will be performed with data obtained at baseline and discharge, followed by multiple correlation analyses using delta scores of the data and, finally, multiple regression analyses again using delta scores. As in objective 2, each of the main outcomes from functioning measurements will be introduced in the models as dependent variable, CS measurements as independent variables, and sex, age and other demographic characteristics and/or test-related variables as potential confounders and/or moderators.

Confounders entering the final models of objectives 2 and 3 will be selected based on their partial correlation coefficient with CS and functioning, and they will be included if p≤0.10. All multiple regression models will have the assumptions checked. Results of objectives 2 and 3 will be reported as coefficient (b), CIs (95% CI), p values and explained variance, with and without controlling for confounders and/or moderators. Due to the large amount of correlation analyses and the risk of high type I error, a stricter significance level for correlation analyses is established, p<0.01. For multiple regression analyses the significance level is at 0.05.

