
Data collected for this project are large and the measurements of CS and functioning collected involve a broad amount of variables. As a result, proxies will be used for the statistical analyses. Previous research in CS assessments, on the one hand, and in functioning assessments, on the other, have reported different methodologies and outcome parameters. The reason for which, even if authors have selected the proxy variables based on their relevance and/or contribution to the purposes of the current studies, the selection of the following measurements as proxies may not be beyond debate: for HRV the RMSSD, as it is a measurement of the parasympathetic/vagal tone which is not influenced by breathing^108^; for the maximal aerobic capacity the VO_2_max corrected for the body mass of the individual, due to the effect of body mass on VO_2_max; and for PA the daily VM counts, because it characterises movement duration and intensity.^109^

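### Daily VM counts rise with hours of accelerometer wear, and wear time reaches the physical-activity models only if it happens to pass a significance screen

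*Protocol article*

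**What the plan says.** The Analyses section names one proxy per functioning domain. For PA it is "the daily vector magnitude (VM) counts for PA". The Discussion gives the reason: "for PA the daily VM counts, because it characterises movement duration and intensity".

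Under PA levels, patients "wear the accelerometer attached at their hip level for 1 week continuously during walking hours" (presumably waking hours), "in order to ensure the minimum of 4 full-day recordings". The article gives no length in hours for a full day. The same section lists other outputs, among them "The daily and weekly time in hours and percentage of time spent in each of the activity intensity categories", so recorded time is available from the device.

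For objectives 2 and 3 the regression covariates are "sex, age and other demographic characteristics and/or test-related variables as potential confounders and/or moderators". For confounders the entry rule is that "they will be included if p≤0.10", judged on partial correlations with CS and functioning. Results are reported with and without this control. Objective 3 uses simple differences between baseline and discharge, computed also for confounders recorded on both occasions.

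**The concern.** A count accumulated over a day is roughly activity rate multiplied by hours worn. The device is not worn round the clock, so hours differ between patients, between days, and between the baseline and discharge weeks. That variation becomes part of the outcome.

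Two consequences are possible. If patients with more CS signs wear the device for fewer hours, the CS-PA association is partly or wholly produced by wear. If wear is unrelated to CS, it is noise and pulls a true association towards zero. Objective 3 is the more exposed: differencing cancels stable activity but keeps any change in wearing habits, which is then read as a change in activity.

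This is a stated choice of outcome, named in Analyses and defended in the Discussion, and not merely processing detail left to another document. The article does scale its neighbouring proxy, dividing VO2max by body mass because body mass affects it. The PA proxy has no counterpart for wear time.

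**Working it through.** **The plan's own figures.** The article states no figure on wear time or VM counts. The regression sample size reproduces: a test of 3 out of 8 predictors, f² = 0.15 (the usual value for a medium effect, assumed), alpha 0.05 and power 0.80 gives N = 77, and 77/0.7 = 110. Nothing below changes either number.

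**Assumed inputs.** Mean wear 14 h; between-patient SD of wear 1 to 2 h; log-SD of activity rate 0.3; wear and rate independent. None of these comes from the documents.

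**Model.** Daily counts = rate × wear. With CVw and CVr the coefficients of variation of wear and rate,

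share of outcome variance due to wear = CVw² / (CVw² + CVr² + CVw²·CVr²).

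CVr² = exp(0.3²) − 1 = 0.0942.

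- SD 1 h: CVw² = (1/14)² = 0.0051; share = 0.0051/0.0998 = 5.1%; correlation of wear with counts = √0.051 = 0.226.
- SD 2 h: CVw² = (2/14)² = 0.0204; share = 0.0204/0.1165 = 17.5%; correlation = √0.175 = 0.419.

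**Wear related to CS, true rate not.** Spurious CS-PA r = (wear-CS r) × (wear-counts r).

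- Low end: 0.2 × 0.226 = 0.045.
- High end: 0.3 × 0.419 = 0.126.

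So about 0.04 to 0.13. For a single simple association, a spurious r of 0.10 reaches p<0.05 in about 14% of studies at N = 77 and 18% at N = 110, instead of 5%. At the 0.01 level used for correlations the figures are about 4% and 6%, instead of 1%.

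**Wear unrelated to CS.** A true r is multiplied by √(CVr²/total), which is √(0.0942/0.0998) = 0.97 at SD 1 h and √(0.0942/0.1165) = 0.90 at SD 2 h. A true r of −0.245 would appear as −0.24 to −0.22.

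**Does the p≤0.10 screen catch it?** With Fisher's z, controlling for sex and age, the chance that a true wear-CS correlation of 0.2 passes is about P(Z > 1.645 − 0.2027·√(N−5)): 53% at N = 77 and 67% at N = 110. At 0.3 (atanh 0.3095) it is about 84% and 94%. These figures concern the CS side only; the rule also looks at the correlation with functioning.

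**Objective 3.** Assume further a baseline-to-discharge correlation of 0.7 to 0.9 for rate and 0.5 to 0.7 for wear. Approximately,

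share of change-score variance due to change in wear = CVw²(1−ρw) / [CVw²(1−ρw) + CVr²(1−ρr)].

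With the product terms kept, the share runs from about 5% (SD 1 h, ρr 0.7, ρw 0.7) to about 48% (SD 2 h, ρr 0.9, ρw 0.5). At SD 1.5 h and ρr 0.8 it is 15% to 22%.

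**The case against.** The strongest reply is that the plan already has a route for wear time. It provides for test-related covariates, and a wear-CS correlation observed at 0.2 or more would meet p≤0.10 at either sample size (about 0.08 at N = 77, 0.04 at N = 110). Change scores are also foreseen for confounders measured twice. A reader might infer that the plan leaves no room for wear-time adjustment; that is not so. What remains is that wear time is not named, that a true correlation of 0.2 fails the screen in a third to nearly half of studies, and that the unadjusted results stay uncorrected.

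Second, the article never uses the word total, and a fuller plan may define a valid day. That is fair, but the stated rationale of duration plus intensity points to an accumulated quantity, and days above any minimum length would still differ.

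Third, the instruction to wear the device throughout waking hours limits the spread. This stands. Contrasting a 10 h with a 16 h day would overstate the problem, since 10 h lies 2 to 4 SD below the assumed mean. 14 h against 12 h gives 14/12 = 1.167, or 17% more counts at equal rate.

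Fourth, counts per minute discard the duration that the authors wanted, and short wear may reflect time in bed, which is genuinely less activity. This also stands, and argues against simply replacing the proxy by a rate.

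Finally, it is tempting to set the bias against the r of 0.25 in the Sample size section. That value sizes objective 1 only, the correlations among CS instruments, where PA does not enter; objectives 2 and 3 rest on a medium regression effect.

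**Conclusion.** The point holds in a limited form. The PA proxy carries wear time into the outcome and the objective 3 change score, and the plan adjusts for it only conditionally. Under the assumed values, the spurious CS-PA correlation is about 0.04 to 0.13 if wear time correlates 0.2 to 0.3 in absolute value with CS; if it does not, the effect is slight attenuation. The documents neither show that such a correlation exists nor give the spread of wear time, so they do not support a claim that the PA results will be biased. The change is worth making because it is cheap and the data are already recorded. It is not a flaw that undermines the study, and the sample size is unaffected.

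**What to change.** Keep daily VM counts as the PA proxy. In every PA regression and partial correlation, include mean daily valid wear time as a covariate regardless of the p≤0.10 screen; for objective 3, include its change between baseline and discharge. Report two sensitivity analyses: VM counts per minute of valid wear, and daily counts without wear-time adjustment.

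The cost is a sentence or two in the plan and one additional predictor in the PA model, with no new data collection. The substantive downside is that, if shorter wear partly reflects more time in bed, adjustment may remove some true difference in activity. Comparison with the unadjusted sensitivity analysis would show this.
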